## 8.2 Regulatory status of the drug

Bovactant was developed by Boehringer Ingelheim. In 1989, it received regulatory approval in Germany for prevention of RDS based on 8 clinical studies (detailed summary is included in the Investigator Brochure: Appendix II and reports on file at Lyomark Pharma and Aerogen Pharma). The regulatory approval was renewed on 9 September 2004.

In 2005 it was acquired by the current manufacturer, Lyomark Pharma (Oberhaching, DE). Since its original approval in Germany, SF-RI 1 (under the marketing name of Alveofact) has been approved in six European countries and in 24 countries outside the EU. The legal manufacturer of Alveofact, following post-marketing requirements, is following the safety profile and according to their most current Post-Marketing report, there are no safety trends or concerns based on self-reporting from centres using the drug.

## 8.3 Regulatory Status of Device

AeroFact-COVID™ is a non-CE marked device. AeroFact-COVID replaces the standard vibrating mesh plate with an alternative of novel architecture but identical material construction as the commercially available Aerogen® Solo nebulizer (K133360, K103635 and K070642, Aerogen Ltd.) This novel “PDAP” mesh is capable of effectively nebulizing pulmonary surfactant, which is otherwise challenging to aerosolize, and generates smaller droplets 1 to 4 microns in size which enhance deep lung delivery. The nebulizer is driven by a small, pole-mounted controller (mains with battery back-up; UK version available), and can be fitted into an endotracheal tube adapter, a mouthpiece or a face mask for treatment of invasively ventilated or spontaneously breathing patients.

The device is a combination of CE-Marked devices and Investigational Devices, with reusable or disposable components:

### Reusable Components:

Areogen Nebulizer Cable – CE Marked  
AC/DC Adapter – CE Marked  
Aerogen Controller Bracket – CE-Marked  
AF-COVID Controller – Investigational Device  
AF-COVID Synchronizer – Investigational Device  
Sensirion Flow Sensor SFM3300 Cable – Investigational Device

### Disposable Components:

AF-COVID Nebulizer: Areogen Solo Nebulizer Housing – CE-Marked  
AF-COVID Nebulizer: Areogen 15mm T-Piece Connector to the Endotracheal Tube – CE-Marked  
AF-COVID Nebulizer: PDAP Mesh – Investigational Device  
Sensirion Flow Sensor SFM3300 – Investigational Device

## 8.4 Product Characteristics

### Bovactant (Alveofact®)

The finished dosage form is a SF-RI 1 lyophilizate that contains no additional excipients and hence has the same chemical composition as the drug substance. The labelled dose in each Type 1, clear glass, 6R vial is 108 mg. The closure is a gray butyl rubber, fluoropolymer-coated, 13 mm stopper with an aluminum/propylene, blue, 13 mm flip-off seal. The current manufacturing facility is BAG Health Care (BAG) GmbH, [name].

As a natural animal derived surfactant preparation, absolute compositional and structural formulae cannot be provided as in the case of a synthetic preparation. It is isolated from bovine lung lavage and, by weight, is a mixture of:

- Phospholipids, approximately:
  - 75% phosphatidylcholine (PC, also known as lecithin)
  - 13% phosphatidylglycerol (PG)
  - 3% phosphatidylethanolamine (PE)
  - 1% phosphatidylinositol (PI)
  - 1% sphingomyelin
- 5% Cholesterol
- 1% lipid-soluble surfactant-associated proteins, SP-B and SP-C
- Very low levels of free fatty acid, lyso-phosphatidylcholine and water
- 0.3% calcium

### AeroFact-COVID Device

The AeroFact-COVID™ Nebulizer is a vibrating mesh nebulizer that is operated electronically by a signal generated continuously with the AF-COVID Controller. The drug is delivered to the mesh nebulizer directly by dispensing into the medication reservoir.

The system generates aerosol with a droplet size distribution smaller than conventional nebulizer systems. Particle size distribution <5 µm mass median aerodynamic diameter (MMAD) was chosen to minimise deposition in tubing and airways, to maximize the potential dose reaching the lungs and to minimise interpatient variability. The nebulizer is positioned between the ventilator circuit and the endotracheal tube or artificial airway, ensuring direct patient drug delivery to minimise drug loss and drug emissions. The system is designed to generate aerosol in synchrony with delivered breaths

during mechanical ventilation, rather than continuously. The delivery rates are up to 0.3 mL/min when used with SF-RI 1 surfactant suspension. The mean delivery rate during breath-synchronized operation is slower than this due to interruption in synchrony with typical Inspiration: Expiration (I: E) ratios.

The AF-COVID system is based on CE-marked components with modifications improving its performance to answer the current clinical need for delivery of aerosolized surfactant into the lungs of adult patients infected with COVID-19 and showing ARDS symptoms.

#### 8.4 Drug storage and supply

Both the vials of lyophilized SF-RI 1 and pre-filled sterile syringe containing 0.45% saline should not be stored above 30°C (86°F) and should not be allowed to freeze. Once the drug product has been reconstituted with 0.45% saline, the resulting suspension can be stored up to 4 hours at 2-8°C or room temperature. In such cases, the vial containing the suspension should be gently inverted 5 times before use. Study medication will be stored in a secure, controlled-access location at the study sites.

Any deviations from the storage conditions should be reported immediately to the Sponsor, and the study medication should be placed in quarantine and not used until authorisation has been given by the Sponsor to do so.

The storage conditions of the re-usable controller and the single-patient, single use disposable, drug delivery circuit and breath sensor are:

Temperature: -20 to +60°C  
Relative humidity: 15 – 95 %RH  
Atmospheric pressure 450 – 1100 kPa

For the AF-COVID clinical development program, SF RI 1 will be sourced from Lyomark Pharma GmbH and supplied to the clinical study sites as a lyophilized formulation of 108 mg, along with the required diluent for reconstitution, and labelled for clinical investigational use only.

#### Storage conditions for the device

The storage conditions of the re-usable controller and the single-patient, single use disposable, drug delivery circuit and breath sensor are:

Temperature: -20 to +60°C  
Relative humidity: 15 – 95 %RH  
Atmospheric pressure 450 – 1100 kPa

Aerogen Pharma will provide the AeroFact AF-COVID investigational product.

Both IMPs and devices will be sent directly to each site Pharmacy from the relevant supplier. Pharmacy will be responsible for recording receipt of product and devices and for dispensing to the Investigator for trial use.

The Investigator (or designee) is responsible for ensuring study medication and device accountability, including administration records and returns. The Sponsor will provide study medication accountability forms for this purpose.

Unused study medication or devices must not be discarded without authority from the Sponsor or used for any purpose other than the present study.

## 8.5 Preparation and labelling of Investigational Medicinal Product

Alveofact® lyophilized vials (108 mg) and pre-filled sterile syringe containing 0.45% saline come ready to be mixed. Once the drug product has been reconstituted with 0.45% saline, the resulting suspension can be stored up to 4 hours at 2-8°C or room temperature. The vials and syringes will be labelled in accordance with regulatory requirements.

## 8.6 Preparation and labelling of Investigational devices

The contents of the label will be in accordance with all applicable regulatory requirements.

In App 3 of the Device Technical File, are the Labels for AF-COVID Devices:

- 1.- Investigational Reusable controllers:
  - a) AF-COVID Controller Device Label
  - b) AF-COVID Synchronizer Device Label
  - c) AF-COVID Controller & AF-COVID Synchronizer Kit Box Label
- 2.- Investigational Disposable Components:
  - a) AF-COVID Nebulizer Device Label
  - b) AF-COVID Nebulizer Pouch and Box Label
3. CE Marked Disposable Components:
  - a) 15mm T-Piece

## 8.7 Dosage schedules

Sequential vials of 108 mg Alveofact® in 2.2 mL buffer will be administered by nebulizer at 5-minute intervals with observation of vital signs, changes in oxygen saturation, FiO2 and Mean Airway Pressure. After each administration, 2 drops of normal saline will be nebulized, and the next vial administered. After administration of the first dose, dosing of Alveofact® will pause and vital signs and ventilation parameters will be assessed over the next 8 hours. If no grade 3 or grade 4 adverse events attributable to surfactant administration occur, another dose of Alveofact® will be administered and vital signs and ventilation parameters will be assessed over the next 16 hours. Again, if no grade 3 or grade 4 adverse events attributable to surfactant administration occur; a final dose of Alveofact® will be administered.

The dosing schedule for each group is displayed in the table below.

| Group | 0 Hours           | 8 Hours           | 24 Hours          |
|-------|-------------------|-------------------|-------------------|
| 1     | 10 x 108 mg vials | 10 x 108 mg vials | 10 x 108 mg vials |
| 2     | 10 x 108 mg vials | 10 x 108 mg vials | 30 x 108 mg vials |
| 3     | 10 x 108 mg vials | 30 x 108 mg vials | 30 x 108 mg vials |
| 4     | 30 x 108 mg vials | 30 x 108 mg vials | 30 x 108 mg vials |

If a dose time point is missed it should be administered as soon as it is possible. The investigator or delegate will assess the clinical stability of the patient prior to administering the dose or following a time point being missed or treatment being suspended.

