## 8 **TRIAL TREATMENTS**

## 8.1 Name and description of investigational medicinal product(s) and device

The AeroFact-COVID™ (AF-COVID) is an investigational drug/device combination product. The proposed indication for the AeroFact-COVID™ combination product is for the treatment of COVID-19 related Adult Respiratory Distress Syndrome (ARDS) in intubated, mechanically ventilated adults.

IMP: Bovactant (Alveofact®) is a lyophilised bovine lung surfactant presented as a lyophilized powder in 108 mg vials and reconstituted to 45 mg/mL in buffer supplied in a prefilled syringe.

Device: The nebulizer, AeroFact-COVID™ Device, is an investigational device based on the Aerogen® Solo, the market-leading vibrating mesh nebulizer for use in critical care and manufactured in Ireland by Aerogen®. It is approved in more than 75 countries and sold in excess of 2 million units in 2019.

AF-COVID combination product consists of three basic components: (i) drug, a lyophilized SFRI 1 bovine-origin surfactant and diluent for reconstitution in a vial with a reconstitution kit (marketed as Alveofact®1 by Lyomark GmbH (Germany)); (ii) reusable components: a Controller, a Synchronizer, AC/DC Adaptors and Cables; and (iii) disposable, single patient use nebulizer and respiration sensor.

Further information on Alveofact and AeroFact-COVID Device can be obtained from the Investigation Brochure and the Device Technical File.

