## 8.7 Dosage modifications

In an event when the administration of 30 vials is not practical, doses may drop to 20 or 10 vials, depending on feasibility. In the event clear efficacy is observed in cohort 1, doses may drop below 10 vials or dosing times may be reduced.

Progression and dosing modifications of subsequent cohorts will be decided by teleconference of the trial steering committee. Any safety concerns would be referred to the independent DSMB on completion of dosing of each cohort of 3 patients + 24 hours to enable collection of physiological outcomes.

The DSMB will actively monitor emerging safety and efficacy data to make recommendations about early study closure or the initiation of a larger randomised controlled clinical trial.

The dose administered cannot be modified due to patient / personal legal representative request.

Given the severity of the illness in ventilated Covid-19 patients, safety data will be interpreted with caution and will not be formally compared between active intervention and control groups.

- Dosing will be stopped in individual patients upon persistent deterioration of oxygenation during or after surfactant administration
- Study stopping rules for futility or efficacy are provided in the statistical analysis section.
- The protocol team will review emerging AE/SAE/SADEs data daily. If 3 or more patients develop the same SAE after administration of study drug, the study will be paused pending review by the DSMB. The study may also pause at the discretion of the Principal Investigator if there are a significant number of unexpected AEs/SAEs/SADEs and referred to the DSMB for review.
- The DSMB will formally review the safety data after every three subjects and is available for ad hoc reviews for other safety concerns as noted above.

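### The 5-minute vial interval and the 8 h and 16 h post-dose assessments do not fit the device's stated maximum delivery rate

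*Protocol*

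**What the plan says.** Section 8.7 (Dosage schedules) describes each vial as 108 mg in 2.2 mL and says that vials "will be administered by nebulizer at 5-minute intervals", with a short saline nebulisation between them. Section 8.1 describes the product as "reconstituted to 45 mg/mL in buffer supplied in a prefilled syringe".

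Doses are due at 0, 8 and 24 h. Section 4 and the Section 8.7 table give these vial counts:

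| Cohort | 0 h | 8 h | 24 h | Total |
|---|---|---|---|---|
| 1 | 10 | 10 | 10 | 30 |
| 2 | 10 | 10 | 30 | 50 |
| 3 | 10 | 30 | 30 | 70 |
| 4 | 30 | 30 | 30 | 90 |

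After the first dose has been given, "vital signs and ventilation parameters will be assessed over the next 8 hours". Dose 2 follows only if no attributable Grade 3 or 4 event has occurred. A 16 h assessment with the same condition precedes dose 3.

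Section 8.4 (AeroFact-COVID Device) states: "The delivery rates are up to 0.3 mL/min when used with SF-RI 1 surfactant suspension". It adds: "The system is designed to generate aerosol in synchrony with delivered breaths", and "The mean delivery rate during breath-synchronized operation is slower than this". It gives neither that mean rate nor an inspiration-to-expiration (I:E) ratio.

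The second Section 8.7 (Dosage modifications) provides that if 30 vials prove impractical, "doses may drop to 20 or 10 vials, depending on feasibility". Section 3.3.1 sets the co-primary endpoints 48 h after study initiation. Section 10 analyses the change 24 h after the last dose and tests response against total dose, with 30/50/70/90 vials as the columns of the power table.

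**The concern.** The dosing section and the device section give figures that cannot both be followed if vials start every 5 minutes. Two things depend on this.

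The first is the check between doses. It is a safety condition for giving the next dose, and its length is fixed in hours after administration, while the next dose is fixed in hours on the trial clock. Once a dose itself takes hours, the two definitions separate, and most of all in the highest-dose cohort.

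The second is the efficacy analysis. The 48 h endpoint and the endpoint 24 h after the last dose coincide only if the last dose is timed from its start. If dosing time grows with the number of vials, the interval from the end of treatment to measurement differs by dose level, and dose level is the explanatory variable in the test. If 30-vial doses are reduced because they take too long, the spread of total doses behind the power table also narrows.

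**Working it through.** **Inputs.** V = 2.2 mL per vial (Section 8.7). r = 0.3 mL/min, an upper limit (Section 8.4). g = 5 min (Section 8.7). D is the share of time in which aerosol is generated: 1 is the ceiling, and otherwise D = I/(I+E), for which the protocol gives no value.

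**The stated pace, read start to start.** 10 vials × 5 min = 50 min; 30 × 5 = 150 min = 2.5 h.

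**The same pace against the device ceiling.**
- Time per vial: 2.2 / 0.3 = 7.33 min. In 5 min the device delivers at most 0.3 × 5 = 1.5 mL.
- Rate needed for one vial in 5 min: 2.2 / 5 = 0.44 mL/min, which is 0.44 / 0.3 = 1.47 times the maximum.
- 10 vials: 73.3 min (1.22 h). 30 vials: 220 min (3.67 h).
- If 108 mg at 45 mg/mL means 108 / 45 = 2.4 mL per vial, the figures become 8.0 min per vial and 4.0 h for 30 vials. The 2.2 mL used here is the more favourable input.

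**If 5 minutes is a pause between vials.** Time = n × V/(r × D) + (n − 1) × g. For 30 vials at the ceiling: 220 + 29 × 5 = 365 min = 6.1 h. There is no pace conflict on this reading, but the dose is longer.

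**Assessment windows, at the ceiling without pauses.**
- Cohort 4, times from the start of a dose: 8 − 3.67 = 4.3 h at most remain after dose 1, not 8 h.
- Cohort 4, times from the end of a dose: dose 2 starts no earlier than 3.67 + 8 = 11.7 h.
- Cohorts 3 and 4, a 30-vial dose started at 8 h ends at 11.7 h or later: 24 − 11.67 = 12.3 h at most remain, not 16 h.
- After a 10-vial first dose the shortfall is smaller: 8 − 1.22 = 6.8 h at most.

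**Endpoint timing, taking study initiation as the first dose.** A 30-vial dose started at 24 h ends at 24 + 3.67 = 27.7 h or later. The 48 h measurement is then at most 48 − 27.67 = 20.3 h after dosing ends in cohorts 2 to 4. In cohort 1 it is at most 48 − 25.22 = 22.8 h.

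**Range under assumed I:E ratios (30 vials; none is given in the protocol).**

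| D | No pauses | 5 min pauses |
|---|---|---|
| Ceiling | 3.7 h | 6.1 h |
| 50% (I:E 1:1) | 7.3 h | 9.8 h |
| 33% (I:E 1:2) | 11.0 h | 13.4 h |

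Without pauses, a 30-vial dose exceeds 8 h only if D < 220/480 = 46% (I:E longer than about 1:1.2). It exceeds 16 h only if D < 220/960 = 23% (I:E longer than about 1:3.4). With pauses, the 8 h threshold is 220/(480 − 145) = 66%.

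**Power if doses are reduced.** The power table was first reproduced by simulating the maximum of linear and Emax contrasts on the log scale, with 12 controls and 3 patients per cohort. A one-sided 5% test and an Emax half-effect dose of 20 vials were assumed. The 0/10/20/30/40% row at CV 20% gives about 0.90 against the stated 0.89. Eleven of the twelve rows agree within 0.02, and the other is 0.65 against 0.63. That row's effect was then read along its own straight line from 10% at 30 vials to 40% at 90:

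| Totals (vials) | 12 controls (table) | 8 controls (Section 4) |
|---|---|---|
| 30/50/70/90, as planned | 0.90–0.91 | 0.85 |
| 30/50/70/80, cohort 4 first dose at 20 | 0.87 | 0.81 |
| 30/50/70/70, cohort 4 first dose at 10 | 0.83–0.84 | 0.76 |
| 30/40/50/60, every 30-vial dose at 20 | 0.65–0.66 | 0.57 |

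Ranges show the spread between simulation runs.

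**The case against.** This is an exploratory pilot in which delivering the doses is itself a feasibility outcome. The protocol expects practical limits. It calls nebulisation time-consuming, says what to do when a dose time is missed, and allows 30 vials to fall to 20 or 10. The interval wording can also be read as a pause. All of that stands and limits how far the point reaches. It does not remove it: a fallback for impractical doses does not say which of two incompatible clock rules governs the next dose, and the pause reading makes the 30-vial dose longer.

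A reader might go further in four ways that the documents do not support.

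- *That a 30-vial dose probably takes 7 to 11 h.* That range follows only from an assumed I:E of 1:1 to 1:2. The protocol says only that the synchronised rate is slower.
- *That the 70- and 90-vial levels cannot be delivered.* Only cohort 4 has a 30-vial dose before the 8 h gap, and without pauses that gap is overrun only below a 46% duty cycle. Cohort 3 has 16 h after its first 30-vial dose, enough up to an I:E of about 1:3.4 without pauses.
- *That the between-dose safety check disappears.* Sections 7.7 and 8.7 keep recording between vials, hourly recording after doses, a stability assessment before dosing, and stopping on persistent deterioration. The post-dose window shrinks.
- *That power collapses.* The fall to about 0.65 (0.57 with 8 controls) needs every 30-vial dose to be cut to 20, including those at 24 h with no later dose to meet. A cut of all of them to 10, leaving every cohort at 30 vials, is further still from what the timing implies. The 8 h conflict concerns only cohort 4's first dose.

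**Conclusion.** The contradiction holds on the protocol's own figures and needs no assumed ratio. Read start to start, the 5-minute pace is impossible in every cohort, because it needs 47% more than the maximum rate. Read as a pause, it makes a 30-vial dose last at least 6.1 h. On either reading cohort 4 cannot have both its second dose at 8 h and 8 h of assessment after its first. The 16 h assessment after a 30-vial dose in cohorts 3 and 4 loses at least 3.7 h. In cohorts 2 to 4 the 48 h endpoint is not 24 h after dosing ends.

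This is wrong as written rather than detail left for later, because it governs a safety condition between doses and the time point of the main analysis. Whether a 30-vial dose overruns the 8 h gap depends on a duty cycle that the protocol does not give. The effect on power depends on how far the fallback is used: from about 0.90 to 0.87 or 0.84 if only cohort 4's first dose is reduced, with the table's 12 controls and the test assumptions stated above.

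**What to change.** Reconcile Section 4, Section 7.7, Section 8.4, both sections numbered 8.7, and Section 10 so that they state:

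- the expected time per vial and per dose at the mean breath-synchronised rate, with that rate and the volume per vial;
- whether the 5 minutes is a start-to-start interval or a pause between vials;
- whether 0, 8 and 24 h, and the 24 h after the last dose used in Section 10, run from the start or the end of a dose;
- an assessment period before each next dose that is consistent with those definitions.

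If the reduction to 20 or 10 vials is expected to be used, restate the power table for the totals that would then be given, with the planned number of controls.

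No view is taken here on which dose, interval or assessment period is right; that is for the sponsor and investigators. The cost is a figure for the synchronised rate, wording changes in the sections named, and a rerun of the power simulation. The drawback is that the stated power may become less favourable.

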### 6.2 Exclusion criteria

1. Imminent expected death within 24 hours
2. Specific contraindications to surfactant administration (e.g. known allergy, pneumothorax, pulmonary hemorrhage)

3. Known or suspected pregnancy
4. Stage 4 severe chronic kidney disease or requiring dialysis (i.e., eGFR < 30)
5. Liver failure (Child-Pugh Class C)
6. Anticipated transfer to another hospital, which is not a study site within 72 hours
7. Current participation or participation in another study within the last month that in the opinion of the investigator would prevent enrollment for safety purposes
8. Consent declined

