## **7 TRIAL PROCEDURES**

### **7.1 Recruitment**

#### **7.1.1 Participant identification**

Hospitalised patients aged  $\geq 18$  that require endotracheal intubation will be considered for inclusion in the study.

Potential patients will be identified by an existing member of the patient's clinical care team. Participant medical records will be reviewed for consideration of inclusion / exclusion criteria. A delegated investigator will confirm inclusion / exclusion prior to enrolling a patient on the study.

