## 7.10 Withdrawal criteria

Withdrawal from the study will only occur if the patient or personal legal representative withdraws consent or safety event in the opinion of the investigators.

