| Adverse Event (AE)                            | Any untoward medical occurrence in a participant to whom a medicinal product has been administered, including occurrences which are not necessarily caused by or related to that product.                                                                                                                                                                                                                                                                                                                                                                                                                                                                                                                                                                                                                                                                                                    |
| Adverse Reaction (AR)                         | 
An untoward and unintended response in a participant to an investigational medicinal product which is related to any dose administered to that participant.
 
The phrase "response to an investigational medicinal product" means that a causal relationship between a trial medication and an AE is at least a reasonable possibility, i.e. the relationship cannot be ruled out.
 
All cases judged by either the reporting medically qualified professional or the Sponsor as having a reasonable suspected causal relationship to the trial medication qualify as adverse reactions. It is important to note that this is entirely separate to the known side effects listed in the SmPC. It is specifically a temporal relationship between taking the drug, the half-life, and the time of the event or any valid alternative aetiology that would explain the event.
 |

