## 16. APPENDICES

## 16.1 Appendix 1

### Schedule of Procedures Screening – Day 13

| Procedures                                        | Screening | Baseline / Treatment Phase |         |          |          | Follow Up |          |    |    |    |    |    |    |     |     |     |     |
|---------------------------------------------------|-----------|----------------------------|---------|----------|----------|-----------|----------|----|----|----|----|----|----|-----|-----|-----|-----|
|                                                   |           | D0                         | 8 Hours | 16 Hours | 24 Hours | (48 hrs)  | (72 hrs) | D4 | D5 | D6 | D7 | D8 | D9 | D10 | D11 | D12 | D13 |
| Informed consent                                  | X         |                            |         |          |          |           |          |    |    |    |    |    |    |     |     |     |     |
| Inclusion / Exclusion                             | X         |                            |         |          |          |           |          |    |    |    |    |    |    |     |     |     |     |
| Demographics                                      | X         |                            |         |          |          |           |          |    |    |    |    |    |    |     |     |     |     |
| Medical history                                   | X         |                            |         |          |          |           |          |    |    |    |    |    |    |     |     |     |     |
| Urine Pregnancy Test                              | X         |                            |         |          |          |           |          |    |    |    |    |    |    |     |     |     |     |
| Vital signs & Ventilation Parameters  | X         | X                          | X       | X        | X        | X         | X        | X  | X  | X  | X  | X  | X  | X   | X   | X   | X   |
| Concomitant medications                           | X         | X                          | X       | X        | X        | X         | X        | X  | X  | X  | X  | X  | X  | X   | X   | X   | X   |
| Diagnostic PCR for SARS-CoV-2 in TA               |           |                            |         |          |          |           | X        |    | X  |    |    |    |    | X   |     |     |     |

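### The conditions for doses 2 and 3 do not include the protocol's own contraindications, so a patient with a new pneumothorax or pulmonary haemorrhage can still qualify for another dose

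*Protocol*

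**What the plan says.** **At entry.** Exclusion 2 in section 6.2 reads "Specific contraindications to surfactant administration (e.g. known allergy, pneumothorax, pulmonary hemorrhage". It sets no minimum grade and does not ask about cause. Section 7.1.1 fixes when this is checked: "A delegated investigator will confirm inclusion / exclusion prior to enrolling a patient on the study". In the Appendix 1 schedule the row "Inclusion / Exclusion" is marked at screening and nowhere else.

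**Before doses 2 and 3.** Section 8.7 (Dosage schedules) says "If no grade 3 or grade 4 adverse events attributable to surfactant administration occur, another dose of Alveofact® will be administered", and applies the same test to the last dose after a further 16 hours. The same section adds "The investigator or delegate will assess the clinical stability of the patient prior to administering the dose", in a sentence that also covers missed time points and suspended treatment.

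**Stopping.** Section 8.7 (Dosage modifications) says "Dosing will be stopped in individual patients upon persistent deterioration of oxygenation during or after surfactant administration". Section 7.10 allows withdrawal from the study for a "safety event in the opinion of the investigators".

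**Recording.** Section 9.2 lists on-study pneumothorax and pulmonary haemorrhage among the respiratory deteriorations, without any consequence for dosing. Section 2.1.2 names pneumothorax as a risk of the drug and device combination.

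**The concern.** The protocol calls these conditions contraindications to giving surfactant, and surfactant is given three times. At the first dose their mere presence is enough to keep the patient out. At the second and third, the question becomes whether an event was severe enough and was caused by surfactant. Neither question bears on whether it is safe to nebulise into a lung that now has a pneumothorax or is bleeding.

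Attribution is a particularly weak filter here, because every patient is ventilated and has severe COVID-19, so another explanation is always to hand. Severity is weak too. Section 9.3.1 grades events by their effect on everyday activities, which means little in a sedated patient, and the table there defines grades 1 to 3 only, although the dosing rule refers to grade 4.

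At stake is a further 10 or 30 vials given, within the written rules, to a patient with a condition the protocol names as a contraindication.

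**Working it through.** The protocol states no figure on this point to reproduce. The check is a comparison of rules, followed by a short calculation of what each later dose commits the patient to.

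**Comparison.** Take a new pneumothorax or pulmonary haemorrhage arising after dose 1 or dose 2.

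| Rule | Where | Trigger | Would it hold the next dose? |
|---|---|---|---|
| Exclusion 2 | 6.2; timing in 7.1.1 and Appendix 1 | Presence of the condition | Not applied again after screening |
| Dose gate | 8.7 Dosage schedules | Grade 3 or 4, and attributable to surfactant | No, if grade 1 or 2, or if judged not attributable |
| Individual stop | 8.7 Dosage modifications | Sustained worsening of oxygenation | No, if oxygenation is preserved |
| Stability assessment | 8.7 Dosage schedules | None stated | At the clinician's discretion |
| Withdrawal | 7.10 | Investigators' opinion | At discretion, and it ends participation rather than holding one dose |
| Event list | 9.2 | Occurrence of the event | No dosing consequence stated |
| Study pause | 8.7 Dosage modifications | Same SAE in 3 or more patients | Not a rule for the individual's next dose |

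An event that is below grade 3, or not attributed, and that leaves oxygenation intact, passes every rule with a stated trigger. Only the two discretionary rows remain.

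**Can attribution fall outside the gate?** Section 9.1 sets a low bar: a causal link counts if it "is at least a reasonable possibility, i.e. the relationship cannot be ruled out". But the scale in 9.3.2 permits a rating of not related where a different cause suffices to account for the event, and 8.7 does not say which ratings count as attributable. The low bar narrows the gap on attribution without closing it, and it does nothing for events of grade 1 or 2.

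**Number of later doses**, from the 8.7 dosing table with 3 treated patients per cohort:

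- Cohort 1: 3 × 2 = 6 doses of 10 vials.
- Cohort 2: 3 doses of 10 vials and 3 of 30.
- Cohort 3: 3 × 2 = 6 doses of 30 vials.
- Cohort 4: 3 × 2 = 6 doses of 30 vials.

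Doses of 10 vials: 6 + 3 = 9. Doses of 30 vials: 3 + 6 + 6 = 15. Total: 24.

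**Minimum nebulising time**, with 2.2 mL per vial (8.7) and the maximum delivery rate of 0.3 mL/min (8.4, Product Characteristics):

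- Per vial: 2.2 / 0.3 = 7.33 min.
- 10 vials: 73 min. 30 vials: 220 min.

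Reconstituting 108 mg to 45 mg/mL implies 108 / 45 = 2.4 mL per vial, which gives 80 and 240 min. All of these are lower bounds: section 8.4 says that breath-synchronised delivery is slower than the maximum, and the pauses between vials are not counted.

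**The case against.** The strongest reply is that neither dosing rule claims to be exhaustive. A contraindication to administration can naturally be read as applying at every administration, so the text contains no outright contradiction. A clinician assesses the patient before the dose, and a chest ultrasound is required before each one (7.7; Appendix 1, footnote 7), so fresh lung imaging is available. Vital signs and ventilation are recorded between vials, and the oxygenation stop applies during administration, so 220 minutes is not an unbroken commitment. For a wrong dose to be given, several safeguards must fail in the same patient within about a day, among 12 treated patients. Most intensivists would hold the dose unprompted. Sections 2.1.2 and 7.7 also refer to the Investigator's Brochure, the Device Technical File and the Instructions for Use, which may contain a warning.

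Much of this stands. It limits the size of the problem and keeps the point minor. It does not remove the point, because no safeguard names these conditions or ties an ultrasound finding to the decision to dose. A small, well-tolerated pneumothorax is also the presentation in which a patient can look stable. The gate says the next dose is given when its test is passed, and that test uses the wrong trigger. If investigators are expected to hold the dose, section 8.7 should say so. Section 10 reports adherence of later doses to protocol criteria, and a dose rightly withheld for a pneumothorax has no clear place under the present criteria.

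**Conclusion.** The concern holds as a minor design flaw in the protocol text. The written conditions for doses 2 and 3 can be met by a patient with a condition that section 6.2 calls a contraindication. The gap is confined to new events that are lower grade or not attributed, with preserved oxygenation, in a patient whom the clinician judges stable.

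The protocol gives no rate for either condition, so the size of this group cannot be estimated; it is expected to be small. The 24 later doses and the minimum times of 73 and 220 minutes describe the exposure at each decision, not harm. They assume that escalation runs as planned and that 30-vial doses are not cut to 20 or 10 vials, as 8.7 (Dosage modifications) allows. The conclusion concerns the protocol alone, since the Brochure and device documents were not available.

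**What to change.** Add one or two sentences to section 8.7 (Dosage schedules):

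- Before the 8 h and 24 h doses, including a delayed dose, the exclusion 2 conditions are re-checked as part of the existing stability assessment. The scheduled pre-dose ultrasound serves for pneumothorax, and clinical findings for pulmonary haemorrhage and allergy.
- Any new such condition, whatever its grade or attribution, suspends dosing until it has resolved, or until it has been reviewed and dosing is judged safe.
- The decision is recorded in the eCRF.

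This keeps clinical judgement, and a treated pneumothorax need not bar dosing for good. What changes is that the hold becomes mandatory and the review is documented. The cost is one pre-dose eCRF item and no new procedure, since the ultrasound and the assessment are already required. The downside is that a few doses may be delayed or omitted.
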